##### Back and leg pain will be measured using the NPRS

The NPRS ranges from 0 (“no pain”) to 10 (“representing worst pain imaginable”). The numerical pain rating scale is reliable, valid, and has good sensitivity (Williamson & Hoggart, 2005).

##### Functional status will be measured with Roland Morris Disability Questionnaires

Five Roland Morris Disability Questionnaires (RMDQ‐24) items were removed and four new items were added from the initial source of RMDQ items, to create RMDQ‐23 (Bergner, Bobbitt, Carter, & Gilson, 1981). RMDQ‐23 consists of 23 “yes” or “no” questions, measuring limitation in activity associated with back and leg pain (Kent, Grotle, Dunn, Albert, & Lauridsen, 2015). The scores can range from 0 (*no disability*) to 23 (*maximal disability*). It has been extensively used in radiculopathy and stenosis research as a standardized measure and is widely used to assess disability specific to back and leg pain making it suitable people with LRS (Kent et al., 2015). The RMDQ‐23 is regarded as reliable and valid (Yamato, Maher, Saragiotto, Catley, & McAuley, 2017). It has been translated into Dutch.

##### Health‐related quality of life (EQ‐5D‐5L and SF‐12)

The EQ‐5D‐5L is a quality of life scale that is responsive for chronic low back pain patients (Soer, Reneman, Speijer, Coppes, & Vroomen, 2012). The EQ‐5D‐5L has five health dimensions: mobility, self‐care, daily activities, pain/discomfort, and anxiety/depression. Within each dimension, the patients can self‐rate their level of severity; no, slight, moderate, severe problems, unable to perform, or do the task (Versteegh et al., 2016). For the economic evaluation, the patients' EQ‐5D‐5L health states will be converted into utility scores ranging from 0 (“death”) to 1 (“optimal health”) using the Dutch tariff (Versteegh et al., 2016).

The SF‐12 is a shorter version of the SF‐36 health‐related quality‐of‐life questionnaire. The SF‐12 has been proven to be a reliable and valid questionnaire for low back pain (Xuemei et al., 2003). The questionnaire relates to the analysis of the general functional status of patients. It consists of 12 questions from the following eight domains: (a) physical functioning, (b) physical role limitations, (c) emotional role imitations, (d) social functioning, (e) physical pain, (f) general mental health, (g) vitality, and (h) general health perception. These eight domains can be summarized into a physical and psychological main domain (Xuemei et al., 2003). For the economic evaluation, quality‐adjusted life years will be calculated by multiplying the patients' time spent in a certain health state by the respective utility value (i.e., area under the curve method).

##### Self‐perceived recovery will be measured using the global perceived effect

The global perceived effect measures a patient's self‐perceived recovery using a 7‐point scale ranging from “worse than ever” (1) to “completely recovered” (7). Being recovered will be defined as being “completely recovered” or “much improved”; other responses will be defined as not recovered. The test reliability of the global perceived effect scale is said to be good (Kampera et al., 2010).

##### Societal and health care costs

Societal costs include costs of the intervention, other health care use, informal care, unpaid productivity losses, and costs due to absenteeism (i.e., sickness absence) and presenteeism (i.e., being less productive while being at work). Health care costs will only include costs accruing to the formal Dutch health care sector.

Intervention costs will be microcosted. For this purpose, information about the combination therapy will be gathered using a case report form, including information on patient classification, number of sessions, discharge, and referral to a network MDT or to the surgeon. All other cost categories will be measured using cost questionnaires administered at baseline 2, 4, 6, 9, and 12 months after randomization. Resource use will be valued in accordance with the Dutch manual of costing (Hakkaart‐van Roijen, Tan, & Bouwmans, 2010). See Table 1: overview of the data collection.

**Table 1 pri1796-tbl-0001:** Overview of the data collection

Outcome measures	Baseline	4 weeks	2 months	4 months	6 months	9 months	12 months
Prognostic factors							
Patient demographics and prognostic factors	X						
Primary outcome							
Surgery rate			X	X	X	X	X
Secondary outcomes							
Pain leg (NPRS)	X	X	X	X	X	X	X
Pain back (NPRS)	X	X	X	X	X	X	X
Health‐related quality of life (EQ‐5D‐5L and SF‐12)	X		X	X	X	X	X
RMDQ‐23	X		X	X	X	X	X
Self‐perceived recovery (GPE)			X	X	X	X	X
Societal and health care costs (cost questionnaires)	X		X	X	X	X	X
Patient satisfaction, complications, and pain location	X		X	X	X	X	X

Abbreviation: NPRS, numeric pain rating scale; RMDQ, Roland Morris Disability Questionnaires.

### Procedure

2.4

#### Treatment allocation

2.4.1

Randomization will be done by an independent researcher who is not involved in treatment procedures, using a web‐based randomization program. The randomization sequence is developed centrally. Therefore, the independent researcher does not have any influence on the randomization procedure, and the treatment allocation is concealed. Patients will be randomized at the individual level and in a 1:1 ratio. We will stratify on duration of complaints (i.e., <6months vs. ≥6months), and we will use one randomization list per hospital. The randomization key will be safeguarded by an independent researcher. Patients allocated to the intervention group will be called for an appointment within 48 hr of randomization and will attend their first appointment within the first week following randomization.

#### Combination therapy intervention

2.4.2

While being on the waiting list to receive lumbar disc surgery, intervention group participants will receive the combination therapy. The combination therapy has two parts (a) MDT and (b) TESIs and is delivered by teams of pain interventionists and physiotherapists. The pain interventionist is responsible for the TESIs and the physiotherapists for the MDT. Prior to receiving the combination therapy, patients are seen by a pain interventionist who checks for contraindications for injections and medications including steroid use. During the same appointment, participants are classified as “centralizers” or “noncentralizers” using MDT principles, that is, assessment of the patients' pain pattern responses on repeated movement tests.

##### Centralizers

Centralizers are defined as patients with centralization (i.e., a clear change in leg pain location from a more peripheral location towards a more central location, which lasts after testing staying in neutral) or directional preference (i.e., a reduction in pain intensity, but not in location, which lasts after testing staying in neutral). Testing for centralization is done according to MDT principles as described in the textbook of McKenzie and May (2003). Searching for centralization is done during repeated movement testing or sustained positioning in a certain direction. This direction differs in patients. Centralization could be found in extension, flexion, side gliding, rotation, or a combination. While testing, an MDT trained physiotherapist is able to decide how many repetitions are needed (usually between 10 and 20) and can add manual force (therapist overpressure or mobilization) if needed, depending on pain response, during and after testing. The MDT system appears to have acceptable interrater reliability for classifying patients with back pain into main/subsyndromes, when applied by therapists who have completed the credentialing examination, but unacceptable reliability in other therapists (Garcia et al., 2018). Sustained positioning is often used with high levels of leg pain and major movement loss in range of motion testing. If a certain direction is found to centralize the leg and back pain, that same direction of exercise or positioning will be used as the initial treatment direction. Patients are advised to exercise seven to eight times a day (i.e., 10 repetitions of extension in lying eight times per day). In the process of centralization, patients get postural advice in the direction of centralization (i.e., if extension is the centralizing direction, patients will be advised to keep their back in lordosis and avoid flexion movements for a period of time). As soon as centralization is full and stable, the physiotherapist trained in MDT will restore full function and most importantly check for fear avoidance of the restricted movement direction, as this could be the case after avoiding a certain direction for a period of time.

##### Noncentralizers

Noncentralizers are defined as patients with peripheralization (i.e., a clear change towards a more peripheral leg pain location or an increase in leg pain) or no effect (i.e., no change in leg pain location or intensity). The hypothesis is that in these patients, the pain is a result of the inflammation. Noncentralizers will receive a transforaminal epidural injection in accordance with the procedure described below.

##### Procedure for the TESIs

The patient lies in prone position. Under fluoroscopic guidance with contrast medium (Iohexol 240 mg/ml 0.5 cc), a very thin needle will be placed next to the compressed nerve. The contrast medium is then used to control if fluid will come to the compressed nerve. After which a combination of a local anaesthetic (lidocaine 20 mg/ml 0.5 cc) with an anti‐inflammatory agent (dexamethasone 20 mg/ml 0.5 cc) is injected. Half an hour after the injection, the pain interventionist checks the effects of the injection. The duration of pain absence is dependent on the working of the anti‐inflammatory drug on the inflammation. Two weeks after the injection, the patient is seen back by the MDT therapist to check for classification in the described subgroups and to decide if a second injection is necessary in shared decision making with patient and the pain interventionist. If pain reduction is less than 80%, then usually, a second injection will be administered with patient consent. A maximum of three injections are given to optimize pain relief.

##### Following TESIs

After the injections, participants will be reclassified using the same MDT principles, into four subgroups. The subgroups are as follows:
resolved symptoms (i.e., no or irrelevant pain; ≤1 on a 0–10 NPRS);centralizing and significantly less pain (i.e., a pain reduction of ≥2 on a 0–10 NPRS);noncentralizing and significantly less pain (i.e., a pain reduction of ≥2 on a 0–10 NPRS); andnoncentralizing with high levels of pain and disability (i.e., a pain score of ≥8 on a 0–10 NPRS and a disability score of >10 on the RDMQ‐23).In the first three subgroups mentioned here, patients will get specific MDT exercises and advice. These three subgroups will be treated by an MDT therapist in one to six sessions in on average 4 weeks. If more sessions are required, patients are referred to accredited MDT therapists within the Rugpoli network. Network therapists are in close contact with the Rugpoli centres and are located all over the Netherlands.

Only the patients in Subgroup 4 will be referred back to the neurosurgeon who will assess whether patients still require surgery. Throughout the combination therapy, there is shared decision making.

#### Control intervention

2.4.3

Control group participants will solely be placed on a waiting list and scheduled to receive lumbar disc surgery if still required. The aim of surgery is to remove the symptomatic disc herniation by a minimal unilateral transflaval approach with magnification, with the patient under general or spinal anaesthesia.

#### Use of cointervention

2.4.4

Use of cointerventions by patients is allowed and will be monitored. Patients will be requested to complete questionnaires in which medication usage and any health care utilization is recorded throughout the follow‐up period.

#### Blinding

2.4.5

We will not attempt to blind the patients to the intervention or control condition, as this is practically impossible in this study due to the nature of the intervention. The outcomes assessor will not be blinded, because all outcomes are self‐reported. Treatment providers (i.e., surgeons, physiotherapist, and anaesthesiologists) will not be blinded due the nature of the intervention they will provide to patients.

#### Sample size

2.4.6

We expect that 90–95% (93% was used in the sample size calculation) of the patients in the usual care group will receive surgery, and we hypothesize that in the combination group, this rate will be reduced by 30% (or more). To detect this difference of 30% with an alpha of 0.05 (two sided), a power of 95%, anticipating a 20% drop‐out rate and taking into account the multilevel structure (with an Intraclass Correlation Coefficient (ICC) of 0.15), we need to include a total of 146 patients (*n* = 73 per treatment group; Pocock, 1983; Twisk, 2006). Even though participants will not be randomized at the hospital level, the multilevel structure of the data was accounted for in the sample size calculation, because patients are recruited from different hospitals (i.e., patients recruited from one hospital are likely to be more similar than those recruited from other hospitals) and clusters will likely not be balanced.

#### Statistical/data analysis

2.4.7

Baseline characteristics of the patients in both study groups will be presented using descriptive statistics (mean [standard deviation], median [range], or proportion) to assess if balanced groups were obtained after randomization (i.e., having an equal distribution of the main outcome measures, prognostic factors, and known confounding factors such as age, gender, educational level, and treatment expectation).

#### Primary outcome analysis

2.4.8

The primary analysis will be an intention‐to‐treat analysis. The primary study parameter (i.e., surgery; yes/no) will be analysed in a logistic mixed model with responses at 2, 4, 6, 9, and 12 months. In this analysis, we will take into account the levels of hospital, patient, and time of measurement. An odds ratio with 95% confidence interval between the combination therapy group and usual care group will be calculated. If necessary, the analysis will be adjusted for important prognostic characteristics.

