#### Primary outcomes measure

2.3.2

The primary outcome measure is the proportion of LRS patients undergoing lumbar disc surgery during 12‐month follow‐up. Patients will be scored as either having had a lumbar surgery or not. For this purpose, patients will be asked whether they had a lumbar surgery during the previous weeks following the last assessment, using an online questionnaire at 2, 4, 6, 9, and 12 months after randomization, and validated using hospital records.

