#### Economic evaluation

2.4.10

An economic evaluation will be performed from a societal and a health care perspective. When the societal perspective is applied, all costs and consequences relevant to the intervention will be taken into account irrespective of whom pays or benefits, whereas only those accruing to the formal Dutch health care sector will be considered when the health care perspective is applied (Hakkaart‐van Roijen, van der Linden, Bouwmans, Kanters, & Tan, 2015; Brouwer, van Exel, Baltussen, & Rutten, 2006).

The economic evaluation will be performed in accordance with the intention‐to‐treat principle and in terms of quality‐adjusted life years as well as the primary outcome proportion of LRS patients undergoing lumbar disc surgery during 12‐month follow‐up. Missing data will be imputed using multiple imputations by chained equations. The imputation model will be constructed in accordance with the recommendations of White, Royston, and Wood (2011). Imputed datasets will be analysed as specified below, after which pooled estimates will be estimated using Rubin's rules (White et al., 2011). Incremental cost‐effectiveness ratios will be calculated by dividing the difference in costs by that in effects. In order to account for the possible clustering of data, analyses will be performed using linear mixed models (Gomes et al., 2012). Accounting for the possible clustering of data (e.g., at the hospital level) is very important, as most economic evaluations fail to do so, whereas ignoring the possible clustering of data might lead to inaccurate levels of uncertainty and inaccurate point estimates (Gomes et al., 2012). Bootstrapping techniques will be used to estimate the uncertainty surrounding the cost‐effectiveness estimates. Uncertainty will be shown by plotting cost‐effect pairs on cost‐effectiveness planes and by constructing cost‐effectiveness acceptability curves (Black, 1990; Drummond, Sculpher, Torrance, O'Brien, & Stoddart, 2005; Fenwick, O'Brien, & Briggs, 2004). Cost‐effectiveness acceptability curves indicate the probability of an intervention being cost‐effective compared with a control for a range of ceiling ratios (i.e., the maximum amount of money decision makers are willing to pay per unit of effect gained).

Various one‐way sensitivity analyses will be performed to test the robustness of the study results (e.g., complete‐case analysis and per‐protocol analysis).

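### The primary model treats surgery by 12 months as five repeated responses with one pooled odds ratio, so it does not estimate the proportion that the trial defines and powers

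*Protocol article*

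**What the plan says.** Section 2.3.2 (Primary outcomes measure) defines the outcome over a follow-up of 12 months: "The primary outcome measure is the proportion of LRS patients undergoing lumbar disc surgery during". On scoring, the same section states: "Patients will be scored as either having had a lumbar surgery or not". That is one binary result per patient. The data come from questionnaires at 2, 4, 6, 9 and 12 months, in which "patients will be asked whether they had a lumbar surgery during the previous weeks following the last assessment", checked against hospital records.

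Section 2.4.6 (Sample size) plans on 93% operated under usual care, reduced by 30% with combination therapy, at two-sided alpha 0.05 and 95% power. With 20% drop-out and an ICC of 0.15 it arrives at 146 patients, 73 per group.

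Section 2.4.8 (Primary outcome analysis) says that surgery yes/no "will be analysed in a logistic mixed model with responses at 2, 4, 6, 9, and 12 months". On the structure of this model it says that "we will take into account the levels of hospital, patient, and time of measurement". The effect is to be reported as a single odds ratio comparing the two arms, with its 95% interval. The section names neither a 12-month contrast nor a treatment-by-time term, and does not say what a response at a visit means.

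**The concern.** Surgery as scored here is once-only: a patient has been operated by 12 months or has not. A repeated-measures logistic model suits states that come and go, such as recovery, and section 2.4.9 applies the same model to those outcomes. For a once-only event, the five responses follow mechanically from the date of operation. The pooled odds ratio then mixes when surgery happened with whether it happened.

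This matters here because timing may differ between the arms. In the combination arm, patients are reviewed two weeks after an injection, may have up to three, and only one of four subgroups is referred back to the surgeon (Procedure for the TESIs; Following TESIs). Surgery may be delayed as well as avoided. The trial's central claim is that surgery is prevented, so the primary analysis must tell the two apart.

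**Working it through.** **The planned figure.** Inputs from section 2.4.6: control 93%; combination 63% if the 30% is absolute, 65.1% if relative (0.93 × 0.70). The stated 73 per group is reached with the relative reading:

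- Unpooled formula: n = (1.960 + 1.645)² × [0.93×0.07 + 0.651×0.349] / 0.279² = 12.995 × 0.2923 / 0.0778 = 48.8, so 49 per arm.
- 49 / (1 − 0.15) / (1 − 0.20) = 72.1, so 73 per arm and 146 in total.

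The ICC step is inferred, as no formula is given. It is a single comparison of two proportions, and no repeated-measures term is among the stated inputs.

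**Target effect.** 12-month odds ratio = (0.63/0.37) / (0.93/0.07) = 0.128, or 0.140 with 65.1%. Evaluable patients: 73 × 0.80 ≈ 58 per arm. A comparison of the 12-month proportions at 58 per arm has 98.1% power (63%) or 96.7% (65.1%), before any ICC allowance.

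**Interval coding (1 in the interval of surgery, 0 otherwise).**

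- An operated patient contributes one 1 and four 0s. Over five responses, 93% becomes 0.93/5 = 0.186 and 63% becomes 0.63/5 = 0.126.
- Crude odds ratio = (0.126/0.874) / (0.186/0.814) = 0.63. With time effects in the model it is 0.51-0.60, depending on assumed timing, against 0.128.
- Responses within a patient are negatively correlated, so the patient variance is estimated at about zero. The model takes the variance of a control patient's total as 5 × 0.186 × 0.814 = 0.757; the true value is 0.93 × 0.07 = 0.065. Without time effects, the standard error under equal arms is too large by √(0.757/0.065) ≈ 3.4.
- Result with time effects, 58 per arm: type I error about 0%; power 61-76% for 93% vs 63%.

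**Cumulative coding (1 from surgery onward).**

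- Each patient's series is 0…0, 1…1 and never reverts. The patient variance runs to whatever bound the software imposes, and only the ratio of treatment effect to patient SD is identified. For 93% vs 63% with proportional timing that ratio is about −0.70, so the odds ratio is about 0.12, 0.03 or 0.0009 at SD 3, 5 or 10.
- Delay registers as an effect. Take 93% operated in both arms, with operations spread over the five intervals as 70/15/8/4/3% (control) and 15/35/25/15/10% (combination). Cumulative proportions are 0.651, 0.791, 0.865, 0.902, 0.930 and 0.140, 0.465, 0.698, 0.837, 0.930; their means are 0.828 and 0.614. The crude pooled odds ratio is (0.614/0.386) / (0.828/0.172) = 0.33, although the 12-month odds ratio is 1.

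Rejection at 58 per arm with cumulative coding and 93% operated in both arms:

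| Assumed delay | Large-variance limit of the mixed model | Pooled model, patient-clustered errors |
|---|---|---|
| None | 5.1% | – |
| Mild | 31% | 18% |
| Moderate | 72% | 53% |
| Strong | 98% | 94% |

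Further pooled runs with clustered errors gave 10% when the share of operations done by 2 months falls only from 70% to 55%, and 96% when it falls from 70% to 15%. The 12-month comparison stays at 4-6% throughout.

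For 93% vs 63%, power in the large-variance limit was 91%, 91% and 47% in three timing scenarios, against 99% for the 12-month comparison. The 47% arises when the arms coincide at 2 months and diverge later.

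The simulations omit the hospital level.

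**The case against.** **Interval coding may not be intended.** The wording about the period since the last assessment describes how the question is put. Section 2.3.2 also scores patients as operated or not, and Table 1 lists the surgery rate at every follow-up visit. Nothing says that an operated patient returns to zero. This stands: the power loss to 60-75% belongs to one reading. Under cumulative coding, power is 91% in two of three scenarios.

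**A third coding exists.** Keeping only patients still at risk gives a discrete-time survival model, which behaves well (4.5% type I error; 98% power for 93% vs 63% with the same timing). But it targets the hazard of surgery and responds to delay, so it does not estimate the 12-month proportion either.

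**An analysis plan could add a 12-month contrast.** It could, and the article does not exclude one. But section 2.4.8 already fixes the model, the five responses and a single between-group odds ratio. Adding the contrast is the correction asked for here.

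**Stronger readings that do not hold.** A reader might infer that the false-positive rate is inflated in general. It is not: with equal timing and equal proportions, rejection is about 5-6% (cumulative) or 0% (interval). Nor is rejection near 95% the general size of the problem; it needs a strong delay, and no waiting time is given. A reader might also see a conflict with the economic evaluation, which uses the "primary outcome proportion of LRS patients undergoing lumbar disc surgery during" 12 months. A clinical odds ratio beside an economic difference in proportions is ordinary practice. Nor is the sample size at fault, since 146 suffices for a 12-month comparison.

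**Conclusion.** The concern holds in this form: the stated primary analysis does not estimate the stated primary outcome. The mismatch lies between sections 2.3.2 and 2.4.6 on one side and 2.4.8 on the other, and needs no assumption. Its size does. Per-interval coding dilutes the odds ratio to about 0.5-0.6 against 0.13 and cuts power to about 60-75%. Cumulative coding leaves the odds ratio without a determinate size. It also rejects in about 10-30% of trials under mild delay and 94-98% under strong delay, although 93% are operated in both arms. These figures assume 58 evaluable patients per arm, no hospital effect and surgery-timing curves that the article does not supply. Because the conclusion about prevention could be wrong in either direction, this should be settled before analysis.

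**What to change.** Make the primary analysis one binary value per randomised patient: any lumbar disc surgery from randomisation to 12 months. Use logistic regression with treatment, the duration-of-complaints stratum and a random hospital intercept, or another method robust to sparse hospitals. Fixed hospital terms are best avoided: with 93% operated in one arm and unbalanced hospitals, some may have no unoperated patient, and their terms could not be estimated. Report the 12-month odds ratio and the risk difference, each with a 95% confidence interval.

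Report time to first surgery (Kaplan-Meier or Cox), or a repeated or discrete-time model with its coding stated, only as a supporting analysis.

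The cost is a minor rewording of section 2.4.8 and the loss of primary inference on timing. The questionnaires and hospital records already planned supply the endpoint, so no new data are needed.

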#### Prognostic factors

2.3.1

Prognostic factors measured at baseline using an online questionnaire include duration and severity of complaints before operation, various psychosocial variables (somatization, distress, and anxiety), and known confounding factors such as age, gender, educational level, and treatment expectation (Kwaliteitsinstituut voor de Gezondheidszorg CBO, 2008).

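### Duration of complaints, a stratification factor, is not named as a term in the primary model, and covariate adjustment is left to an undefined condition; fixing both in advance is a free improvement

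*Protocol article*

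**What the plan says.** Four places in the protocol article bear on this.

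- Treatment allocation (2.4.1): "We will stratify on duration of complaints (i.e., <6months vs. ≥6months), and we will use one randomization list per hospital".
- Prognostic factors (2.3.1): the baseline variables include "duration and severity of complaints before operation". By the plan's own account, the stratification factor is related to outcome.
- Statistical/data analysis (2.4.7): baseline characteristics are described "to assess if balanced groups were obtained after randomization", which is spelled out as "having an equal distribution of the main outcome measures, prognostic factors, and known confounding factors".
- Primary outcome analysis (2.4.8): surgery yes/no goes into a logistic mixed model, with this on its structure: "In this analysis, we will take into account the levels of hospital, patient, and time of measurement". The arms are to be compared by an odds ratio and its 95% interval. The section then ends: "If necessary, the analysis will be adjusted for important prognostic characteristics".

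The secondary outcome section (2.4.9) carries the same approach over to the secondary outcomes. The blinding section (2.4.5) says that patients, treatment providers and outcome assessment are not blinded. It does not mention the analyst.

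**The concern.** An analysis should follow the randomisation. Hospital, one of the two randomisation factors, is in the model. Duration of complaints, the other, is not named there and could enter only through a conditional sentence.

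That sentence does not say what makes adjustment necessary, which characteristics count as important, or when the decision is taken. Any imbalance after proper randomisation is due to chance, so it is a poor reason to adjust. Equally, good balance is no reason to leave out a strong prognostic factor. If the decision is taken after data are seen, the primary result can come from any of several models, and a reader cannot tell whether the choice was influenced by the result. The effect measure is an odds ratio, whose target depends on what is conditioned on, so the open choice also leaves unclear which odds ratio the trial estimates.

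**Working it through.** The plan gives no figure of its own on this point, so the check is a comparison of the text followed by simulation.

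**Text.** Randomisation factors: hospital and duration. Model levels named: hospital, patient, time. Duration is therefore the one randomisation factor not named.

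**Simulation inputs.** From the plan: N = 146, 1:1 allocation, and a surgery rate of 93% under usual care. An 80% rate was run as well, as an assumption. The plan's target odds ratio, reading the 30% reduction as absolute (93% to 63%), is (0.63/0.37) / (0.93/0.07) = 1.703 / 13.286 = 0.128.

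The plan gives no prognostic strengths, so three sets were assumed on the log-odds scale: none; moderate (0.8 for duration, 0.3 for each of four other covariates); strong (1.5 and 0.5). Each simulated trial was analysed by ordinary logistic regression of surgery at 12 months, without dropout and without hospital or patient random effects.

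**Two-sided type I error at nominal 5%:**

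| Rate, strength | Unadjusted | + duration | + duration and 4 others | Adjust only if baseline difference has p < 0.05 | Most favourable of these |
|---|---|---|---|---|---|
| 80%, none | 4.5% | 4.5% | 4.7% | 4.4% | 5.3% |
| 80%, moderate | 4.7% | 5.0% | 5.2% | 4.5% | 6.6% |
| 80%, strong | 4.1% | 5.1% | 5.3% | 3.7% | 7.3% |
| 93%, none | 2.3% | 2.3% | 2.7% | 2.3% | 3.1% |
| 93%, moderate | 3.2% | 3.3% | 4.0% | 3.1% | 4.8% |
| 93%, strong | 3.6% | 4.2% | 4.8% | 3.5% | 6.3% |

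Three results follow.

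1. Leaving out duration is conservative: 4.1% without it against 5.1% with it (80% rate, strong effects).
2. A mechanical imbalance rule does not inflate error: it stays between 2.3% and 4.5%.
3. Only free choice among the models raises the error. At the planned 93% rate it passes 5% only under the strong assumptions.

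**Odds ratio when the true conditional value is 0.128 (93% rate), median estimate:**

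| Strength | Unadjusted | + duration | + duration and 4 others |
|---|---|---|---|
| None | 0.123 | 0.121 | 0.114 |
| Moderate | 0.141 | 0.134 | 0.111 |
| Strong | 0.182 | 0.159 | 0.109 |

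Simulated power was about 99% with or without duration. In the first row the covariates have no effect, yet the largest model still moves the estimate from 0.123 to 0.114. That movement cannot be non-collapsibility and points to sparse data. The larger spread in the other two rows is mainly non-collapsibility.

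**Room for covariates.** Controls expected to avoid surgery: 73 × 0.07 = 5.1, so about 5 before dropout. That supports only a short covariate list.

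**The case against.** The strongest reply is that this is a condensed article and that the sentence on levels describes the multilevel structure, not every fixed effect; treatment is not in that sentence either. Duration may therefore be in the full model, and as a listed prognostic factor it may also enter through the adjustment sentence. This stands in part. A reader might infer that the model contains only hospital, patient and time, but the text does not say so. What remains is that the article does more than stay silent: it writes a conditional rule for adjusting the primary analysis, and a later plan that fixed the covariates would have to replace that rule.

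Four other strong readings also go beyond the documents or the numbers.

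- **That adjustment depends on the balance check.** No sentence says so. The order of the two sections makes it plausible, and no other trigger is offered, but it is an inference.
- **That omitting the stratification factor, or adjusting on imbalance, produces false positives.** The simulation shows neither.
- **That type I error would be 6.7% or 8.5%.** A separate simulation (3,000 null trials, n = 116, linear-probability tests, five covariates with an assumed log odds ratio of 0.5 per SD) gave these figures for the best of two and the best of seven models. The protocol describes no such search, and the same simulation gave 4.6% for the mechanical rule.
- **That the odds ratio is biased towards 1.** The shift is mainly a change of conditional target and is not confounding. It was also obtained without the planned random effects; a patient-level intercept may absorb much of an omitted patient-level covariate.

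**Conclusion.** The point holds in a limited form, as a free improvement. The stratification factor is not named in the primary model, and the adjustment rule has neither a trigger nor a list. Nothing here shows that the planned analysis is invalid: its default, without duration, errs on the safe side.

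The exposure is the open choice of model. The worst case, in which the most favourable model is always picked, is a type I error of about 5–7% at an 80% surgery rate and 3–6% at 93%, together with an odds ratio whose meaning varies with the covariate set. These sizes rest on assumed prognostic strengths and on a single 12-month logistic model without hospital or patient random effects. They indicate the order of magnitude and do not predict what this trial would do. The absence of a stated rule does not depend on them.

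**What to change.** In the primary outcome section, delete the opening condition of the adjustment sentence. State that the primary model includes treatment, hospital (already planned as a level) and duration stratum (under 6 months or longer), fixed in advance and kept whatever the observed balance.

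If further baseline covariates are wanted, name a short list before data are seen; with about 5 controls expected to avoid surgery, a long list would be fragile. Report the analysis without covariates as a sensitivity analysis, and use the baseline table for description only. Since the secondary outcomes follow the same approach, the wording should cover them too.

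The cost is a few lines of text. Duration is already recorded for stratification and the other candidates are on the baseline questionnaire, so no new data are needed and the sample size stays at 146.
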